## Materials and methods

2

### Design

2.1

The study will use a mixed-methods study design and will be conducted at the Inner Mongolia Maternity and Child Health Care Hospital from 2025 to 2026. A randomized controlled trial with two parallel groups will compare the effectiveness of an Artificial Intelligence-Empowered Mobile Health intervention guided by Swanson’s Theory of Caring on psychological distress (such as depression, anxiety, and stress) in women after abortion. The intervention will last for two weeks, with participants undergoing questionnaires, physical examinations, and individual interviews at baseline and at two weeks to explore changes in psychological distress. The study flowchart is shown in **Figure 1**.

**Figure 1 f1:**
[figure not shown]
Flow chart of patient recruitment and study implementation.

The study used a simple randomization method. The steps are as follows: first, in Excel, we used the RAND function to generate a number between 0 and 1. The function is invoked by entering “=RAND()” in any cell and pressing Enter. The generated number determines the group assignment for each patient: if the number is from 0 to 0.5 (excluding 0.5), the patient is assigned to the intervention group; if it is from 0.5 to 1 (excluding 0.5), the patient is assigned to the control group. If the number is exactly 0.5, the process is repeated until a valid random number is obtained.

The blinded method used in this study involves several categories of individuals:

Medical staff in the research department (blinded): responsible for patient recruitment, informing patients of admission and follow-up times and locations, and conducting basic biochemical and imaging examinations for admission and follow-up, they are unaware of patient group assignments.Investigators (blind): Their responsibilities are strictly limited to one-on-one data collection with patients; they do not participate in other research activities to ensure data specificity and accuracy. Investigators are unaware of patient group assignments.Data processing personnel (blind): They receive coded data (Group A/Group B) and are unaware of the specific assignment relationship between Groups A/B and the intervention or control groups.Patients (unblinded): The intervention group is guided by the researcher to follow the Artificial Intelligence-Empowered Mobile Health Official Account and instructed on its use. The control group does not receive this service.System administrator (unblinded): Responsible for online management and answering questions for patients in the intervention group; their service is limited to patients in the intervention group, as only this group receives the Artificial Intelligence-Empowered Mobile Health intervention.

### Study sample

2.2

A total of 100 participants will be enrolled in this study. The participants in this study were female outpatients who undertook surgical abortion at the Inner Mongolia Maternity and Child Health Care Hospital. This study used continuous enrolment, and prior to the study, patient consent was obtained, and patients were randomly assigned to the intervention group and the control group, with 50 patients in each group, for a total of 100 patients. The inclusion and exclusion criteria are as follows:

#### Inclusion criteria

2.2.1

Non-hospitalized patients undergoing surgical abortion before the 14th week of pregnancy;Aged ≥18 years;No history of taking any psychiatric drugs before enrolment;Possession of a smartphone and familiarity with general WeChat functions;Voluntary participation in the study and completion of an informed consent form.

#### Exclusion criteria

2.2.2

Involuntary abortion or unclear pregnancy intentions;Severe physical complications after abortion (such as massive bleeding, infection, etc., requiring hospitalization);Individuals with mobility issues, impaired consciousness, or mental disorders;Individuals with tumors who have undergone radiotherapy or chemotherapy in the past six months;Inability to understand or complete questionnaires in Chinese;Currently participating in other similar research studies;Unwilling to cooperate.

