**Phase 1: From outpatient visit to surgery day.**

**Swanson’s Theory of Caring:** Knowing.

**Intervention providers:** Attending doctor, researcher.

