**Specific Methods:**

1. Detailed Description of Functions:

Artificial Intelligence-Empowered Mobile Health provides the following support:

① Health Education: Answers questions about diseases, such as preoperative preparation, potential complications, recovery time, etc., guides physical recovery, such as the normal range of bleeding days and amounts, indications for medical treatment, etc., provides dietary advice, such as dietary taboos, common dietary misconceptions, etc., provides exercise guidance, such as bed rest time, appropriate types of exercise and timing, etc.

② Entertainment and Emotional Support: Artificial Intelligence-Empowered Mobile Health has personification attributes, can introduce itself during the first interaction, can recognize user emotions and provide comfort and encouragement, and also provides practical tools such as weather queries and simple calculations.

2. Artificial Intelligence-Empowered Mobile Health Usage Process Guidance:

Step 1: Researchers provide one-on-one guidance to patients who meet the criteria and have signed the informed consent form, instructing them to follow the WeChat Official Account for this study on their mobile phones.

Step 2: Guide patients to enter the Official Account and locate the chat interaction page.

Step 3: Under the guidance of the researcher, patients take the lead in operating the Official Account, using text or voice input to experience its health education and emotional support functions.

3. Question Guidance:

Researcher demonstrated common input commands face-to-face, such as “What do I need to prepare for an abortion?” and guided patients on how to ask questions effectively to the Official Account. The researcher provided concise answers to other questions from patients about the system’s functions and operation, and performed live demonstrations of the functions on the patients’ mobile phones.

**Swanson’s Theory of Caring:** Being with, Maintaining belief.

**Intervention providers:** Attending doctor, researcher.

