**Specific Methods:**

Communication Time: One week after the patient’s abortion, online communication via telephone, WeChat, or other platforms, lasting approximately 20 minutes.Communication Content: Comprehensive understanding of the patient’s physical recovery, inquiring about fever, foul-smelling secretions, bleeding, abdominal pain, etc., assessing the patient’s psychological state, whether there are negative emotions such as inferiority, anxiety, depression, or despair, recognizing the patient’s additional needs for post-operative health knowledge.

**Swanson’s Theory of Caring:** Doing for, Enabling.

**Intervention providers:** Researcher.

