What specific functionalities of Artificial Intelligence-Empowered Mobile Health did you use?Which Artificial Intelligence-Empowered Mobile Health functionalities had a positive effect on your health, and which ones had no effect or even had a negative effect?How did using Artificial Intelligence-Empowered Mobile Health affect your mental health? What do you think caused these effects?With the help of Artificial Intelligence-Empowered Mobile Health, what did you learn about post-abortion care?To what extent did you trust the health information provided by Artificial Intelligence-Empowered Mobile Health? Did you find its responses reliable? Why?’How did you feel when Artificial Intelligence-Empowered Mobile Health attempted to comfort or encourage you? Do you perceive this emotional support as genuine? Please elaborate on your feelings.”What were your expectations of Artificial Intelligence-Empowered Mobile Health prior to using it? How did its actual performance differ from your expectations?’Compared to support provided by healthcare professionals or family/friends, what unique aspects did you find in interacting with Artificial Intelligence-Empowered Mobile Health? Which form of support do you prefer? Why?’

Patient demographic information will be collected through the case system and self-designed questionnaires. (**Table 1**).

**Table 1 T1:** Variables and measures collected at every time point.

Variables	Date source	Measures	Baseline(T0)	Post-intervention(T1)
Intervention preparation	/	Eligibility screen, Informed consent and Allocation	✓	
Covariates	Baseline questionnaire	Sociodemographic information	✓	
	Baseline questionnaire and Follow-up questionnaire	Behavioral information	✓	✓
Primary outcome	Baseline questionnaire and Follow-up questionnaire	Patient Health Questionnaire-9 (PHQ-9)	✓	✓
Secondary outcome	Baseline questionnaire and Follow-up questionnaire	Generalized Anxiety Disorder-3, GAD-3	✓	✓
		Perceived Stress Scale 4, PSS-4	✓	✓
		Perceived Social Support Scale Short Form, PSSS-SF	✓	✓
		Body Image-Acceptance and Action Questionnaire-5, BI-AAQ-5	✓	✓
		Posttraumatic Stress Disorder Checklist for DSM-5, PCL-5	✓	✓
		EuroQol Visual Analogue Scale, EQ-VAS	✓	✓
	Clinical examination and laboratory tests	Ultrasound, human chorionic gonadotrophin, HCG		✓
Qualitative results	semi-structured interviews	Effect of the trial		✓

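### The exclusion for severe complications after abortion cannot be assessed at baseline: on the plan's own timeline it can be met only after randomisation, and it would remove randomised women if applied as written

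*Protocol article*

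**What the plan says.** The exclusion criteria (2.2.2) include "Severe physical complications after abortion (such as massive bleeding, infection, etc., requiring hospitalization".

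On timing, the article says the following:

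- Inclusion criteria (2.2.1): the population is "Non-hospitalized patients undergoing surgical abortion before the 14th week of pregnancy".
- Study sample (2.2): "prior to the study, patient consent was obtained, and patients were randomly assigned to the intervention group and the control group".
- Table 1: "Eligibility screen, Informed consent and Allocation" is ticked at baseline (T0) only.
- Specific intervention strategies (2.5.4): the first stage is "Phase 1: From outpatient visit to surgery day". In it, women sign consent, complete the electronic questionnaires and are set up on the AI account.
- Control group (2.5.1): the education given at enrolment covers the operation itself and the preoperative examinations.

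Two places read differently. The abstract describes the participants as women after abortion, and section 2.2 puts their surgery in the past tense.

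**The concern.** An eligibility criterion should rest on facts known before allocation. If it depends on something that happens afterwards, applying it makes membership of the compared groups depend on post-baseline events, and the groups are no longer those that randomisation formed.

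Here the event may also be influenced by treatment. The intervention arm gets advice and monitoring directed at complications, and the control arm is not described as getting them. Women hospitalised with bleeding or infection may also be among the more distressed, which would tie the removal to the primary outcome, depression on the PHQ-9.

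**Working it through.** **Step 1. When is allocation known?** No single sentence says that randomisation precedes surgery, so I set the sections side by side.

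- Table 1 puts screening, consent and allocation together at T0.
- In Phase 1, which ends on the day of surgery, women who have consented complete the questionnaires. T0 data collection is therefore preoperative.
- In the same phase the AI account is demonstrated. Its content includes preoperative matters: "Answers questions about diseases, such as preoperative preparation, potential complications, recovery time, etc". The example query shown to patients is about preparing for the procedure.
- The blinding description in section 2.1 says that controls do not get this account, so assignment must be known before it is set up.
- Control education at enrolment (2.5.1) is preoperative too, so the same order holds in both arms.

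The order is therefore: consent, T0 questionnaires and allocation, then the start of the intervention, then surgery, then any complication of that surgery.

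**Step 2. When can the criterion be met?** For the index abortion, only at the last of these stages. It cannot be checked at T0.

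**Step 3. Could it act differently by arm?** These elements are described for the intervention arm only:

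- Section 2.5.3: researchers analyse the interaction data for severe physical symptoms and contact the attending physician when needed.
- Phase 2, one-week contact of about 20 minutes: "inquiring about fever, foul-smelling secretions, bleeding, abdominal pain".
- Phase 2: daily review of the chat records, with key feedback passed to the attending doctor.
- Phase 2: closer contact between patient and researcher, meant to pick up serious problems.

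These could raise the number of hospitalised complications by finding more of them, or lower it by leading to earlier care. The direction cannot be predicted.

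**Step 4. How large could the effect be?** The plan gives no figure to reproduce on this point. The article states only 50 women per arm and a target difference of 5 PHQ-9 points (2.3). The removal proportions and the excess score below are my assumptions.

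Let p_I and p_C be the proportions removed in the intervention and control arms, and let h be the PHQ-9 excess of removed over kept women, taken as equal in both arms. In each arm, full mean = kept mean + p × h. Hence:

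kept difference (intervention − control) = full difference + (p_C − p_I) × h

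- 1 of 50 removed in each arm: (0.02 − 0.02) × h = 0.
- 1 of 50 intervention, 3 of 50 control: (0.06 − 0.02) × 5 = +0.20, and × 8 = +0.32.
- 3 of 50 intervention, 1 of 50 control: −0.20 to −0.32.
- 0 of 50 against 5 of 50: 0.10 × 5 = 0.50, and × 8 = 0.80, with the sign set by the arm that loses more.

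A lower PHQ-9 is better, so a negative shift flatters the intervention. As a share of the 5-point target, 0.20 to 0.32 is 4% to 6.4%, and 0.50 to 0.80 is 10% to 16%.

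**The case against.** **Removal is not stated.** Section 2.2.2 is an eligibility list. Nowhere does the article say that a randomised woman who meets it is withdrawn or left out of the analysis, and analysis sets are commonly left to a full protocol or SAP that is not shown. This stands as a limit: removal is the effect of following the rule, not a declared procedure. It does not rescue the rule, because a criterion that can be met only after allocation is badly fixed whatever the analysis set. The multiple imputation in section 2.7 deals with missing data and does not say how women declared ineligible are treated.

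**Enrolment might follow surgery.** The abstract and one clause in 2.2 can be read that way, and the flow chart is not available. That reading conflicts with Phase 1, the preoperative questionnaires and the control-arm content. The conflicting wording does need to be reconciled.

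**It might refer to an earlier abortion.** This is possible, but nothing in the wording says so.

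**Differential removal is speculative.** Events that need hospital care may surface without a telephone call. Controls also receive advice on postoperative precautions, and blinded staff carry out the follow-up examinations. This is fair: a difference between arms is a possibility, not something established.

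**Stronger readings that the article does not support.**

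- A reader might infer that a safety outcome is being hidden. Section 2.9 requires adverse events to be reported immediately and serious ones within 24 hours, with committee oversight, and exempts nobody who meets this criterion.
- A reader might extend the point to the exclusion for unwillingness to cooperate. That can be judged at screening.
- A reader might charge each removal to the gap between 42 and 50 per arm in section 2.3. The printed formula with its own inputs gives (1.96 + 1.28)² × 2 × 8² / 5² = 53.7, so 54 and not 42. That gap is not a sound allowance to draw on, and the present point does not need it.

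**Conclusion.** The point holds as a matter of timing. On the order of events given by Table 1, Phase 1 and section 2.5.1, the complication exclusion cannot be assessed at T0. Followed as written, it acts on randomised women through a post-baseline event that the intervention might influence.

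The conclusion rests on two inferences: that enrolment is preoperative, which most but not all of the wording supports, and that the criterion means the index abortion.

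The resulting bias has unknown size and direction. Under the assumptions above it runs from zero to about 0.8 PHQ-9 points either way, and 0.2 to 0.3 points for a modest imbalance. That is small against a 5-point target. The reason to act is the validity of the randomised comparison, and the correction is cheap. The article does not support saying that women will in fact be dropped, or that one arm will lose more than the other.

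**What to change.** 1. Delete the complication criterion from section 2.2.2, or limit it to conditions present before randomisation.
2. Reconcile the abstract and section 2.2 with Phase 1 and Table 1, so that one statement fixes when consent, T0 and allocation occur relative to surgery.
3. State that every randomised woman stays in follow-up and is analysed in her assigned arm for the primary outcome, whatever complications occur.
4. Tabulate complications requiring hospitalisation by arm.

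The cost is a short amendment, with no added patients or visits. There is one small practical consequence. Section 2.9 has investigators guide participants one-on-one through the electronic questionnaire in a standardised setting. Women in hospital at T1 may have to complete it elsewhere, so the amendment should allow for this and the setting should be recorded.

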### Sample size

2.3

This study is a mixed-methods research. The intervention group will receive Artificial Intelligence-Empowered Mobile Health interventions, while the control group will receive standard care. Based on previous research findings, nursing interventions based on Swanson’s Theory of Caring have been shown to significantly reduce depression and anxiety levels in women who have experienced abortion, and can serve as a reference for effect size (29). The Minimum Clinically Important Difference (MCID) was selected as a reduction of ≥5 points on the Patient Health Questionnaire-9 (PHQ-9), which is considered clinically meaningful (30). The standard deviation (SD) is based on previous studies showing that the SD of PHQ-9 in the abortion population is approximately 6–8 points. The test level α = 0.05 and test efficacy 1-β = 0.90 are set, and according to the randomized controlled trial mean comparison formula:

$$n=\frac{{\left(Z_{\alpha /2}+Z_{\beta }\right)}^{2}\cdot 2\sigma^{2}}{\Delta^{2}}$$

The sample sizes for each experimental group are equal. Z_α/2_ = 1.96, Z_β_ = 1.28, σ = 8, Δ = 5 in this example. The sample size for each group can be calculated as n = 42 people. Considering the follow-up missing rate, the sample size for each group is increased to 50 people, for a total of 100 people.

Qualitative research is guided by the principle of information saturation, meaning that interviews with patients are stopped once a certain number of participants have been reached and no new information is emerging. Therefore, this study does not specify a minimum sample size for qualitative research.

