#### Qualitative research section

2.4.2

In the quantitative research, two categories of patients were selected based on their baseline PHQ-9 scores: those with higher scores and those with lower scores. The selection process ensured representativeness across key demographic characteristics such as gender and age, resulting in an initial list of interview participants.Prior to the formal interviews, patients were contacted through multiple ways to explain the content of the qualitative research and obtain informed consent, and interview times were scheduled.On the day of the interview, the research objectives, methods, and recording permissions and privacy protection measures were reiterated to the participants. After obtaining consent, the interview was initiated, and a participation gift was provided at the end.

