##### Depression levels

2.6.1.1

In this study, symptoms of depression were assessed using PHQ-9. This scale consists of nine items, each corresponding to the core symptoms of depression in the Diagnostic and Statistical Manual of Mental Disorders (DSM), such as depressed mood, sleep problems, and fatigue (30). Each item is scored on a scale of 0–3 points(0 = “not at all” to 3 = “nearly every day”). The scores for the 9 items are added together, with a total score ranging from 0–27 points. The higher the total score, the more severe the depressive symptoms. The severity of depression is classified according to the total score as follows: 0–4 minimal depression, 5–9 mild depression, 10–14 moderate depression, 15–19 moderate depression, 20–27 severe depression. The Cronbach’s alpha for the Chinese version of the PHQ-9 is 0.86 (32).

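### Section 2.3 uses a PHQ-9 reduction of at least 5 points as the mean difference between arms, but entry sets no minimum score, so Δ = 5 is unsupported and power may fall well below 90%

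*Protocol article*

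**What the plan says.** Section 2.3 (Sample size) chooses the effect in these words: "The Minimum Clinically Important Difference (MCID) was selected as a reduction of ≥5 points on the Patient Health Questionnaire-9 (PHQ-9". It cites an SD range, "the SD of PHQ-9 in the abortion population is approximately 6–8 points", and sets the error rates: "The test level α = 0.05 and test efficacy 1-β = 0.90 are set". The formula for comparing two means is then filled in with "σ = 8, Δ = 5 in this example". The result is given as 42 per group, raised to 50 for loss to follow-up. Earlier nursing studies based on the same theory are named as a reference for effect size, but no figure is taken from them.

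Section 2.6.1.1 scores the PHQ-9 from 0 to 27, with the lowest bands "0–4 minimal depression, 5–9 mild depression".

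Sections 2.2.1 and 2.2.2 list no PHQ-9 or distress threshold for entry. They require "No history of taking any psychiatric drugs before enrolment" and exclude "Individuals with mobility issues, impaired consciousness, or mental disorders". Section 2.4.2 picks interviewees by baseline PHQ-9, "those with higher scores and those with lower scores". No baseline PHQ-9 mean or distribution appears anywhere in the article.

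**The concern.** The threshold in section 2.3 is worded as a reduction, that is, a change within a patient. In the formula, Δ is something else: the difference between two arm means, averaged over every randomised woman. The section gives no step from one to the other.

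The step matters because the scale has a floor. A woman who enters at 0–4 cannot fall by 5, nothing in the entry criteria keeps her out, and the two psychiatric criteria plausibly shift the sample towards low scores. For the average to reach 5, women above the floor would have to gain more than 5 to make up for those who cannot.

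If they do not, a programme that gives 5 points to every woman with room for it would still show a mean difference below 5. The trial could then report a non-significant result, or one below the stated threshold, and the reader could not tell a floor effect from an ineffective intervention.

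**Working it through.** **1. The plan's own figure.** From section 2.3: Z = 1.96 and 1.28, σ = 8, Δ = 5.

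n = (1.96 + 1.28)² × 2 × 8² / 5² = 10.4976 × 128 / 25 = 53.7, so 54 per group, not 42.

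With σ = 7 the same formula gives 10.4976 × 98 / 25 = 41.2, so 42. This discrepancy is a separate matter. It enters here only because it means that the starting power is already below 90% at σ = 8.

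**2. Power with an undiluted Δ = 5.** Two-sided 5% t-test, noncentral t with 2n − 2 degrees of freedom and noncentrality Δ / (s√(2/n)). At n = 50 and s = 8 the noncentrality is 5 / (8 × 0.2) = 3.125.

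| SD | 50 per group | 42 per group |
|---|---|---|
| 6 | 98% | 97% |
| 7 | 94% | 90% |
| 8 | 87% | 81% |

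**3. Assumptions for the floor.** The article gives the SD (6–8) and the range (0–27), but no mean. I assume:
- a beta-binomial score on 0–27 with mean 8, 10 or 12;
- control scores at T1 that follow this distribution;
- a benefit of min(score, 5) for each treated woman, so each gains 5 points or falls to zero.

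The mean difference is then Δ = 5(1 − p) + g·p, where p is the share at 0–4 and g is the mean score in that share. Example at σ = 8 and mean 8: p = 0.467, g = 1.23, so Δ = 5 × 0.533 + 1.23 × 0.467 = 3.24.

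**4. Power with this Δ.** The same model narrows the treated arm, so I use s = √((σ_C² + σ_T²)/2), and show the equal-SD result beside it. In the example σ_T = 6.54, s = √((64 + 42.8)/2) = 7.31, and the noncentrality is 3.24 / (7.31 × 0.2) = 2.22.

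| SD | Mean | Share at 0–4 | Δ | Treated SD | Power, n = 50 (equal SDs) | Power, n = 42 (equal SDs) |
|---|---|---|---|---|---|---|
| 8 | 8 | 47% | 3.24 | 6.5 | 59% (52%) | 52% (45%) |
| 8 | 10 | 34% | 3.86 | 6.8 | 73% (67%) | 65% (59%) |
| 8 | 12 | 23% | 4.28 | 7.1 | 80% (75%) | 73% (68%) |
| 7 | 8 | 41% | 3.60 | 5.8 | 80% (72%) | 72% (64%) |
| 6 | 8 | 35% | 3.95 | 5.0 | 94% (90%) | 90% (85%) |
| 6 | 10 | 21% | 4.45 | 5.3 | 97% (96%) | 94% (92%) |
| 6 | 12 | 12% | 4.73 | 5.6 | 98% (97%) | 96% (95%) |

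**5. What would restore an average of 5.** Without the cap, if women at 0–4 all fall to zero, the others need a mean benefit of (5 − g·p)/(1 − p). At σ = 8 that is 8.3, 6.7 and 5.9 points for means 8, 10 and 12. For mean 8: (5 − 1.23 × 0.467)/0.533 = 4.43/0.533 = 8.3.

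**The case against.** A reader might infer that the floor makes a mean difference of 5 impossible in this trial. The documents do not support that. Δ is a between-arm difference, the threshold is 5 or more, and the scale runs to 27. Women with high scores may gain 8 or 10 points, and a difference can also arise if low-scoring controls worsen after surgery. The values 3.2–4.3 are ceilings only under the 5-point cap, which is my assumption.

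Three further points stand in part:
- **The share at 0–4 is not known.** The Background reports that over 60% of interviewees had occasional or frequent depression and anxiety after abortion. That is not a PHQ-9 distribution, but it warns against assuming a mostly symptom-free sample. Nor does section 2.4.2 say that its lower scorers are at 0–4.
- **A sample crowded near zero may have a smaller SD.** At SD 6 and mean 8 or more, power at 50 per group holds at 90% or above. The large losses belong to the upper part of the cited SD range. The protocol itself, however, chose σ = 8.
- **Section 2.7 plans a longitudinal GEE, not a t-test on final scores.** Baseline used as a covariate would help. At an assumed correlation of 0.5 the SD falls by √0.75, and the 52% (σ = 8, mean 8, equal SDs) becomes 64%. A comparison of changes at that correlation gains nothing, since its variance is 2(1 − 0.5)σ² = σ². The article does not say which contrast is meant.

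Enrolling women without regard to score is also a legitimate choice for a broad support programme. It does not settle what Δ that population can be expected to show.

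**Conclusion.** The concern holds as a gap in the justification of Δ and a conditional loss of power. Section 2.3 equates a within-patient reduction with a population mean difference, in a population that may include women who cannot reach that reduction, and offers nothing to support an average of 5.

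At the protocol's own σ = 8, the stated 90% is not met even with a full Δ = 5 (87% at 50 per group, 81% at 42). With the floor and the 5-point cap it is about 59–80% at 50 per group for baseline means of 8–12. At SD 6 with mean 8 or more, the stated power survives at 50 per group.

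These figures rest on an assumed baseline mean and distribution, the cap, and control scores that stay as at baseline. Correcting the 42 to 54 would not settle the point, because 54 gives about 90% only if the mean difference really is 5.

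**What to change.** Keep n = 100 and change two things.

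1. **Section 2.3.** State that the 5-point threshold refers to an individual's reduction. Give Δ separately, as the between-arm mean PHQ-9 difference over all randomised women. Replace the single 90% figure with power over Δ of about 3 to 5 and SD 6–8, at 50 and 42 per group, and name the baseline distribution assumed. For orientation, with equal SDs and 50 per group, Δ = 3 gives 70%, 56% and 46% at SD 6, 7 and 8; Δ = 4 gives 91%, 81% and 70%.
2. **Section 2.7.** Pre-specify one supportive analysis of the T1 PHQ-9 difference by baseline PHQ-9: either a treatment-by-baseline term, or the difference in women with baseline 5 or more. Label it as low-powered. Its purpose is to let a small overall difference be read against a possible floor effect, not to replace the primary comparison.

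The cost is some rewording and one extra analysis of data already collected at T0 and T1. The downside is a less favourable stated power. No extra patients are needed.

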### Statistical analysis

2.7

After the trial is completed, all collected case data and questionnaire responses will be organized and summarized. Data storage will be managed using Microsoft Office 2017, while statistical analysis will be conducted using SPSS Statistics 27.0 software. Count data will be presented as case numbers (N) and percentages (%). The normality of continuous data will be assessed; normally distributed data will be presented as mean ± standard deviation, while non-normally distributed data will be presented as median (interquartile range) and interquartile range (P25-P75). Appropriate statistical tests (e.g., independent samples t-test, Mann-Whitney U test, and chi-square test) will be used to compare baseline characteristics between the intervention and control groups based on data type. Longitudinal analysis of follow-up data will be conducted using generalized estimating equations (GEE) to compare differences in outcomes between the two groups. Two-sided tests will be used, with statistical significance set at p < 0.05. In cases of missing data, multiple imputation techniques will be applied, considering the randomness of missing data. Multiple imputation involves generating multiple complete datasets by replacing missing values with reasonable estimates derived from observed data and imputation models. Compared to single imputation methods, this approach preserves the variability of the dataset and enhances the reliability of results. Multiple imputation will be performed using established statistical software (e.g., SPSS or R). Sensitivity analysis will also be conducted to assess the robustness of results under various assumptions regarding missing data. This comprehensive approach ensures the validity and reliability of research findings while maintaining statistical integrity throughout the analysis process and accounting for missing data. Qualitative interview audio files will be transcribed verbatim and anonymized, and analyzed using Grounded Theory with NVivo (Version 12, QRS International, Doncaster, Australia). Qualitative and quantitative data will be incorporated to better interpret the results across multiple stages during the trial.

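### The printed sample size of 42 per group does not follow from the printed inputs (σ = 8, Δ = 5, 90% power), which give 54; at σ = 8 the trial falls short of its stated power

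*Protocol article*

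**What the plan says.** The calculation is in section 2.3 (Sample size) of the protocol article. It compares two means using n = (Z_α/2 + Z_β)² · 2σ² / Δ² per group.

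- **Error rates:** "The test level α = 0.05 and test efficacy 1-β = 0.90 are set", with Z_α/2 = 1.96 and Z_β = 1.28. Section 2.7 confirms the sidedness: "Two-sided tests will be used, with statistical significance set at p < 0.05".
- **Difference:** the minimum clinically important difference was "selected as a reduction of ≥5 points on the Patient Health Questionnaire-9 (PHQ-9").
- **Standard deviation:** earlier studies are cited to the effect that "the SD of PHQ-9 in the abortion population is approximately 6–8 points". The values entered are "σ = 8, Δ = 5 in this example".
- **Allocation:** "The sample sizes for each experimental group are equal".
- **Result:** "The sample size for each group can be calculated as n = 42 people".
- **Allowance for loss:** "Considering the follow-up missing rate, the sample size for each group is increased to 50 people, for a total of 100 people". No loss rate is given.

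**The concern.** The formula, all its inputs and its result are printed together, and the result is not what the formula gives. The gap is 12 patients per group (54 against 42, or 22%), too large for rounding. The next step builds on the wrong figure: the increase to 50 is described as cover for missing follow-up, yet 50 is already below the number required with complete follow-up. Under the printed inputs there is no attrition margin.

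PHQ-9 depression is the primary outcome, and this calculation is the only justification for the size of the trial. If the result is null, readers will take it as coming from a trial with a 10% chance of missing a 5-point difference. At the protocol's own σ, that chance is higher.

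**Working it through.** **Inputs** (section 2.3): Z_α/2 = 1.96, Z_β = 1.28, σ = 8, Δ = 5, equal groups.

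**1. The plan's figure from its own formula**

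- (1.96 + 1.28)² = 3.24² = 10.4976
- 10.4976 × 2 × 8² = 10.4976 × 128 = 1343.69
- 1343.69 / 5² = 53.75, so **54 per group**

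The t-test version needs 54.8, so 55. The printed 42 is not reproduced.

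**2. What would give 42**

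| σ | Power | Sides | n per group (formula) |
|---|---|---|---|
| 8 | 90% | 2 | 54 |
| 7 | 90% | 2 | 10.4976 × 98 / 25 = 41.15, so **42** |
| 6 | 90% | 2 | 10.4976 × 72 / 25 = 30.2, so 31 |
| 8 | 80% | 2 | 41 (t-test 41.2, so 42) |
| 8 | 90% | 1 | 44 |

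With the printed formula, Z values and Δ, the only whole-number σ in the cited range that gives 42 is 7. A t-test calculation at σ = 8 and 80% power also rounds up to 42, but it contradicts the printed Z_β and does not use the printed formula.

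**3. Power at σ = 8, Δ = 5**

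Normal approximation: power = Φ(Δ / (σ√(2/n)) − 1.96).

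- n = 42: 5 / (8 × 0.2182) = 2.864; Φ(0.904) = 81.7%
- n = 50: 5 / (8 × 0.2) = 3.125; Φ(1.165) = 87.8%

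The t-test gives 80.8% (n = 42), 87.2% (n = 50), 89.6% (n = 54) and 90.1% (n = 55). The type II error is therefore about 19% with 42 evaluable per group and about 13% with all 50, against the stated 10%.

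**4. Difference detectable with 90% power at σ = 8**

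3.24 × 8 × √(2/n):

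- n = 42: 25.92 × 0.2182 = 5.66 points
- n = 50: 25.92 × 0.2 = 5.18 points

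Both exceed the 5-point difference on which the trial is sized.

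**5. Allowance for loss**

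No rate is printed. Raising 42 to 50 implies 1 − 42/50 = 16%. At that inferred rate, 54 evaluable would need 54 / 0.84 = 64.3, so 65 per group. At an assumed 10%, it would be 54 / 0.90 = 60.

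**6. Largest σ that still gives 90% power (formula)**

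σ = Δ√(n/2) / 3.24:

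- n = 42: 5 × 4.583 / 3.24 = 7.07
- n = 50: 5 × 5 / 3.24 = 7.72

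At σ = 7, power is 90.5% with 42 and 94.6% with 50.

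**7. Effect of baseline adjustment at σ = 8**

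The documents give no baseline–follow-up correlation ρ, so the values below are assumptions. Adjusting for baseline multiplies the required n by (1 − ρ²).

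| Assumed ρ | n per group, 53.75 × (1 − ρ²) | Power with 42 | Power with 50 |
|---|---|---|---|
| 0.3 | 48.9 | 85% | 91% |
| 0.4 | 45.1 | 88% | 93% |
| 0.5 | 40.3 | 91% | 95% |

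Powers use the normal approximation with SD = 8√(1 − ρ²). With 42 evaluable, 90% needs ρ of at least √(1 − 42/53.75) = 0.47. With all 50, it needs at least √(1 − 50/53.75) = 0.26.

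**The case against.** The strongest reply is that σ, not n, is the misprint. A planning SD of 7 lies in the middle of the cited range and gives exactly 42 by the printed formula. Power would then be above 90% with 42 evaluable and nearly 95% with 50, and nothing would be wrong with the trial's size. This is plausible, and the document cannot rule it out. It makes the power shortfall conditional on σ = 8. It does not remove the error: section 2.3 names 8 as the value used, so either σ or n is wrong in print.

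Two further points carry some weight. First, the worst case assumes exactly 42 evaluable per group. With full retention the shortfall is only 2 to 3 percentage points, and no loss rate is printed. However, the plan expects losses and treats 42 as the required number. Second, section 2.7 plans generalized estimating equations on baseline and follow-up data, with multiple imputation, so the final analysis may use information that an unadjusted comparison of completers ignores. That could recover power, but the stated 90% comes from an unadjusted formula with no correlation, so it cannot be credited to such an analysis as written.

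**Conclusion.** The point holds. The printed formula and inputs give 54 per group, not 42, and nothing else in the article corrects this. This part rests on no assumption.

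The consequence for power depends on taking σ = 8, the only SD the protocol says it used, in an unadjusted two-sample comparison. On that basis power is about 81% to 87% (t-test), depending on losses, instead of 90%, and the enrolled 50 per group leaves no margin for loss. If the intended σ was 7, the size is adequate and the error is confined to the printed σ. Either way, section 2.3 needs correction, because a reader cannot tell which number to believe.

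**What to change.** The sponsor should state which SD produced 42, its source, and the loss rate behind the increase to 50. The target of 100 patients can stay, with section 2.3 corrected in one of these ways:

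- **(a) Keep σ = 8.** State that 42 evaluable per group give about 81% power for a 5-point difference, and about 87% if all 50 are analysed. Remove the 90% claim.
- **(b) Correct σ to 7.** This reproduces 42. Justify the value from the cited studies rather than from the result it yields, and report the power at σ = 8 alongside it, since 8 lies in the cited range.
- **(c) Keep both σ = 8 and 90%.** Base the calculation on a baseline-adjusted primary analysis, name that analysis consistently in sections 2.3 and 2.7, and give a sourced baseline–follow-up correlation. It must be at least about 0.47 for 42 evaluable per group.

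Each is a change of wording and needs no extra patients. The cost is a less favourable stated power under (a), and an added assumption to defend under (b) or (c).
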